**Safety endpoints:**

- Incidence of any adverse events or clinically significant laboratory abnormalities
- Vital signs, new physical examination abnormalities
- ECG abnormalities

**Exploratory Endpoints**

The exploratory endpoints are:

- Proportion of patients with PCR-corrected cure on Day 14
- Proportion of patients with PCR-corrected cure on Day 28
- Cure rate on Day 42
- Proportion of patients with PCR-corrected cure on Day 42

Genotyping of *P. falciparum*-specific polymorphic genes by PCR is well established to distinguish recrudescence from new infection. However, in the case

of *P. vivax*, polymorphic molecular markers have not been fully validated. Current molecular tools may identify new infection (or relapse from a previous infection) but cannot distinguish relapse (of current infection) from recrudescence. Endpoints determined by PCR analysis will be regarded as exploratory.

New infection as evidenced by PCR-genotyping studies will be considered as treatment success.

Due to the lack of validated molecular tools, the primary endpoint will be based on a crude cure rate on Day 14. However, the Day 28 data will be collected and analysed as secondary endpoint.

### **9.5.2. Methods of statistical analysis**

A detailed statistical analysis plan will be prepared and documented prior to study unblinding and database lock.

#### **Primary Efficacy Analysis:**

The primary efficacy analysis will test the non-inferiority of the PA group compared to the chloroquine group with regard to cure rate on Day 14 using a two sided 95% confidence interval and a 10% non-inferiority margin and be performed on the efficacy evaluable (EE) population. Non-inferiority will be demonstrated if the lower limit of the two-sided 95% confidence interval (CI) for the difference in cure rates on Day 14 (normal approximation) is not lower than -10%.

The following primary efficacy hypothesis will be tested:

H0: The cure rate on Day 14 for the PA group is inferior to the cure rate on Day 14 for the comparator group by more than 10%.

Versus the alternative

HA: The cure rate on Day 14 for the PA group is NOT inferior to the cure rate on Day 28 for the comparator group by more than 10%.

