## 5. ASSESSMENTS

### 5.1. Efficacy Assessments

#### 5.1.1. Parasitological assessments

##### 5.1.1.1. Microscopy

Parasite density expressed as the number of parasites per microlitre ( $\mu\text{L}$ ) of blood will be measured serially to determine parasite clearance time (PCT). Asexual parasite and gametocyte counts will be recorded separately at screening, while total parasite counts will be recorded at any timepoint thereafter. Blood sampling for parasitology will be done usually by means of finger prick except when the timing for parasitology assessments coincide with time for clinical laboratory tests, in which cases, blood smears (thick and thin) and blood drop for PCR can be taken from the venous blood collected for clinical laboratory analyses.

Blood smears preparation, staining, examination and interpretation should be in accordance with the guidelines provided by the Sponsor. Any deviation from the Sponsor guidelines must be discussed and approved by the Sponsors before the study commences.

Thick and thin blood films for parasite count should be obtained and examined at screening on Day 0 to confirm inclusion/exclusion criteria. Thick blood films will be examined every 8 hours (+/- 1 hour) following first dose administration and for at least 72 hours (Day 1 and Day 2) or until the parasites have cleared as evidenced by two consecutive negative slide readings taken 8 to 24 hours apart. To avoid disruption of patient sleep at night, the first interval between the first dose administration and the next smear may be shorter or longer than 8 hours but shall not exceed 12 hours.

Thick blood films will be also examined on Days 3, 7, 14, 21, 28, 35 and 42 or on any other day if the patient spontaneously returns. Additionally, blood films should be obtained whenever parasitological reassessment is required. A thin blood smear will also be taken from Day 7 whenever parasitological blood samples are taken, and reserved in the event of recrudescence, to confirm *Plasmodium* species.

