### **9.4. Determination of Sample Size**

Assuming a cure rate on Day 14 of 90% in both treatment groups and assuming a non-inferiority limit of -10%, then a sample size of 410 evaluable patients randomized in 1:1 ratio (205 patients in each treatment group) would provide 90% power to demonstrate non-inferiority of PA compared to the chloroquine, using a two-sided 95% confidence interval with Normal approximation. Assuming a drop out rate of 10%, 456 subjects would be randomized to the study (228 subjects in each treatment group).

Assuming a cure rate on Day 14 of 95%, this sample size would provide >99% power to demonstrate non-inferiority of PA compared to the chloroquine.

Sample size estimation was performed using nQuery statistical software version 4.0.

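### The primary Day 14 comparison is valid and adequately powered, but leaving out site, baseline parasite density and age may give up a little precision that costs no extra data to recover

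*Protocol*

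**What the plan says.** Protocol section 9.5.2 (Primary Efficacy Analysis) compares Day 14 cure in the efficacy evaluable population "using a two sided 95% confidence interval and a 10% non-inferiority margin". The decision rests on whether the lower limit "for the difference in cure rates on Day 14 (normal approximation) is not lower than -10" per cent. No baseline variable and no site term is named.

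The candidate covariates are collected regardless. Under section 5.1.1.1, "Asexual parasite and gametocyte counts will be recorded separately at screening". Age is an entry criterion (3 to 60 years), and demography is taken at baseline (section 5.2.1.1). Section 4.1 describes permuted-block randomisation with complete blocks assigned to each site. The same section 9.5.2 uses site as a factor in the analysis of variance of log parasite counts, but not in the primary comparison.

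Section 9.4 sizes the trial on the unadjusted comparison: "Assuming a cure rate on Day 14 of 90% in both treatment groups", "assuming a non-inferiority limit of -10" per cent, and "a sample size of 410 evaluable patients randomized in 1:1 ratio".

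**The concern.** When allocation is blocked within site and cure differs between sites, an interval that ignores site is somewhat wider than the design requires. The same can hold for any baseline value that predicts cure. Adjusting for such values estimates the same risk difference against the same margin, usually with a smaller standard error, and guards against chance imbalance. That matters a little more here because the efficacy evaluable population removes patients after randomisation (section 9.2).

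The documents give qualitative reasons to expect some differences between sites. The Synopsis lists Cambodia, India, Indonesia and Thailand, and the Introduction names India and Indonesia among places with reported chloroquine resistance. What is at stake is efficiency, not validity.

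**Working it through.** **Inputs from section 9.4:** cure 90% in both arms, margin 10 points, two-sided 95% interval, 205 evaluable per arm, 10% dropout.

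**Reproducing the plan's figures.**
- Simple unpooled formula: n = 0.18 × (1.960 + 1.282)² / 0.10² = 189.1, so 190 per arm. This is not the stated 205.
- Farrington-Manning variance: the restricted rates under the null are 0.931 and 0.831, so the null standard deviation is √(0.931×0.069 + 0.831×0.169) = 0.452. Then n = (1.960×0.452 + 1.282×0.424)² / 0.10² = 204.3, so 205 per arm with 90.1% power. This matches.
- Dropout: 410 / 0.9 = 456. This matches.

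**Power of the rule as written at 205 per arm.** SE = √(0.18/205) = 2.96 points and the half-width is 5.81 points. Power = Φ(0.10/0.0296 − 1.96) = 92.1% (91.8% by exact enumeration). At 95% cure it is 99.6%.

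**Idealised effect of adjustment.** The documents give no prognostic strength, so R² (the share of variance in cure explained) is an assumption. Multiplying the variance by (1 − R²) gives half-widths of 5.81, 5.75, 5.66 and 5.51 points at R² of 0, 2, 5 and 10%, and power of 92.1, 92.6, 93.4 and 94.5%. For scale, a combined covariate score with an odds ratio per SD of 1.5, 2 or 3 corresponds to R² of about 1.5, 4.5 or 11%. As an illustration for site alone, assumed cure rates of 80, 90, 95 and 95% at four equal sites average 90% and give R² = 0.00375/0.09, about 4%.

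**Realistic effect.** The idealised formula ignores the cost of estimating the extra coefficients. The table shows simulation of a linear model of cure on arm, two covariates and site at 90% cure and 205 per arm, with five sites assumed (the amendment says 4 to 6) and the prognostic effect carried by one covariate. It gives the width of the adjusted interval relative to the unadjusted one:

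| R² | HC3 variance | HC1 variance |
|---|---|---|
| 0 | 1.5% wider | 0.5% wider |
| about 1.5% | 0.8% wider | 0.2% narrower |
| about 4.6% | 0.6% narrower | 1.6% narrower |
| about 11% | – | 4.0% narrower |

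With HC1, power changes by about 0 at R² = 0 and +1.6 points at about 11%. A repeat run of the same set-up gave +2.1 points at the top, so the last few tenths are simulation noise. In half-width terms, 4% of 5.81 is about 0.23 points and 0.5% is about 0.03 points. In patients, 410/0.96² − 410 is about 35 extra evaluable patients at the top of the range; at R² = 0 the cost is 410 − 410/1.005², about 4 patients.

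A standardised logistic model (two covariates, no site term, 4,000 runs) gave unadjusted versus adjusted power of 91.2 v 91.2% with no effect, 91.5 v 92.1% at an odds ratio of 1.5, 91.8 v 93.0% at 2 and 91.8 v 94.4% at 3.

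**The case against.** The strongest reply is that nothing here is an error. The raw difference is valid under randomisation, estimates the quantity to which the margin applies, matches the sample-size method and exceeds its power target. All of that stands.

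A reader might infer that density and age are known predictors of Day 14 *P. vivax* cure, so that the plan demonstrably wastes precision. The documents do not support this: no section says that either value predicts cure, and none gives an R² or odds ratio. With zero prognostic value, adjustment costs a little instead of helping.

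A reader might also take the idealised narrowing of 1.0, 2.5 and 5.1% at R² of 2, 5 and 10% (from √(1 − R²)) as the expected gain. It overstates the gain, and with an HC3 variance the interval is wider at the low end. This objection stands too, and it is why the variance estimator matters.

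The last argument is that covariates belong to the statistical analysis plan. An extra supportive analysis could indeed wait for it. The primary decision rule, however, is already fixed in the protocol as unadjusted, and section 9 requires departures from the planned analysis to be justified and recorded. The choice can therefore be discussed on the protocol alone.

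**Conclusion.** The point holds as a small, optional gain in precision. The planned analysis need not change to be sound. Site has the clearest basis in the design; density and age are plausible additions whose value is undocumented.

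At 90% cure and 205 per arm, the change runs from a 0.5% wider to an about 4% narrower interval, and from about 0 to +1.6 power points. This rests on an assumed R² of 0 to about 11%, five assumed sites and a linear model with HC1 variance. At 95% cure the unadjusted power is already 99.6%, so almost nothing can be gained. Only a result close to the margin could be decided differently.

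**What to change.** Before unblinding, prespecify as primary the Day 14 marginal risk difference adjusted for site, log10 baseline asexual parasite density and age. Use either a logistic model standardised to a risk difference or a linear model of cure (0/1) with HC1, not HC3, robust variance. Apply the -10% rule to its 95% interval and keep the unadjusted interval as a sensitivity analysis. State the form of each covariate and how small sites are handled, because only about 41 failures are expected among 410 patients at 90% cure (0.10 × 410), and about 20 at 95%.

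The cost is a paragraph of protocol or SAP wording and a few lines of code, with no new data. The downside is a slightly less simple primary analysis and a negligible widening if the covariates turn out not to be prognostic.

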#### **Secondary Efficacy Analyses:**

The primary efficacy analysis performed on Day 14 will be repeated for the proportion of patients with cure on Day 21 and 28, using the efficacy evaluable population.

In addition, the analysis performed using the EE population will be repeated using the ITT population.

The parasite clearance time and fever clearance time will be analysed using Kaplan-Meier estimates. The median and quartiles clearance time will be presented together with the corresponding 95% confidence intervals. The mean will also be calculated. The survival curves will be presented. The log rank test will be used to compare the parasite clearance time and fever clearance time between the two treatment groups. Patients who do not have documented parasite or fever clearance will be censored. Censoring time will be greater than the highest observed clearance time.

The proportion of patients who have parasite clearance and the proportion of patients who have fever clearance will be presented at Day 1, Day 2 and Day 3. The associated exact 95% confidence interval will also be calculated.

The number of parasites will be summarized using standard descriptive statistics, as well as geometric mean and its associated 95% confidence interval using an analysis of variance model on  $\log_{10}$  transformed parasites counts with treatment and site as factors. The mean parasite count at each scheduled timepoint will be presented graphically.

All secondary efficacy analyses will be performed both on the EE and ITT populations.

**Exploratory Analyses:**

The primary efficacy analysis performed on Day 14 will be repeated for the proportion of patients with PCR-corrected cure on Day 14 and 28, using the efficacy evaluable population and the ITT population.

**Safety Analysis**

Safety analyses will be based on the Safety population.

**Adverse Events**

Adverse events (AEs) will be summarized by presenting, for each treatment

group, the number and percentage of patients having any AE, having an AE in each system organ class and having each individual AE (preferred term). Additionally, a summary of adverse events by preferred term and severity will be performed using the worst severity grade.

All related AEs, AEs with outcome death, AEs leading to permanent discontinuation of treatment, SAEs and related SAEs will be summarized by percentages and frequencies and listed including the Investigator term, the preferred term, start and end date of AE, duration (days), severity, drug relationship, action taken and outcome.

Treatment related AEs are those rated by the Investigator as “definite”, “probable”, “possible”. In case relationship is unknown or missing the worst case will be assumed and the AE will be considered to be drug related.

Adverse events will be coded using the latest available MedDRA dictionary version.

### **Laboratory Data**

The incidence of patients with a clinically significant abnormal value as reported by the Investigator will be provided by lab parameter, treatment group and scheduled visit.

For each laboratory parameter, a summary of shift in abnormalities from baseline to each post-baseline visit will be presented. Normal ranges will be used to determine if a laboratory value was normal or not.

Summary statistics will be computed for all safety laboratory parameters. All laboratory values will be converted to SI units.

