### 3.2.2. Exclusion criteria

To be eligible for enrolment in the study, patients must NOT meet any of the following criteria:

1. Presence of a mixed *Plasmodium* infection.
2. Presence of other clinical condition requiring hospitalization.
3. Presence of significant anaemia, as defined by  $\text{Hb} < 8 \text{ g/dL}$ .
4. Known history or evidence of clinically significant disorders such as cardiovascular (including arrhythmia, QTc interval greater than or equal to 450 msec), respiratory (including active tuberculosis), hepatic, renal, gastrointestinal, immunological (including active HIV-AIDS), neurological (including auditory), endocrine, infectious, malignancy, psychiatric or other abnormality (including recent head trauma).
5. Known history of hypersensitivity, allergic or adverse reactions to pyronaridine, chloroquine or artesunate or other artemisinins.
6. Known history of hypersensitivity, allergic or adverse reactions to chloroquine, primaquine and related agents.
7. Known active Hepatitis A IgM (HAV-IgM), Hepatitis B surface antigen (HBsAg) or Hepatitis C antibody (HCV Ab).
8. Known seropositive HIV antibody.
9. Have received any antimalarial treatment in the preceding 2 weeks, as determined by history and, whenever feasible, by screening test.
10. Have received antibacterial with known antimalarial activity in the preceding 2 weeks.

11. Have received any investigational drug within the past 4 weeks.
12. Liver function tests (AST/ALT levels) more than 2.5 times the upper limit of normal range.
13. Known significant renal impairment as indicated by serum creatinine levels of more than 1.4 mg/dL.
14. Female patients of child-bearing potential must be neither pregnant (as demonstrated by a negative pregnancy test) nor lactating, and must be willing to take measures to not become pregnant during the study period.
15. Previous participation in the present clinical trial with pyronaridine artesunate.

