### 5.2.2. Laboratory assessments

Clinical laboratory tests are to be performed as indicated in Table 1.

Haematology parameters are to be measured on Days 0, 3, 7, 28 and 42 and, if clinically indicated, on other visits.

Biochemistry and urinalysis are to be measured on Days 0, 3, 7 and 28, as well as Day 42 if clinically indicated.

Female patients of child-bearing potential will have a urine hCG test for pregnancy prior to inclusion and on Days 14, 28 and 42.

Clinical laboratory tests will require 2 ml for haematology and 2 ml for clinical chemistry, plus a urine sample for dipstick analysis.

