### Entry Laboratory Screen

At a minimum the results of the following tests must be available before the patient is randomised:

- ◆ Haemoglobin
- ◆ Urea
- ◆ Sodium
- ◆ Potassium
- ◆ Blood glucose
- ◆ Alanine aminotransferase (ALT/SGPT)
- ◆ Aspartate aminotransferase (AST/SGOT)
- ◆ Creatinine
- ◆ Pregnancy test (Urine hCG)

If the results of baseline laboratory evaluations of other haematology, biochemistry and urine parameters fall outside of the normal range and are regarded as clinically significant, the Study Medical Monitor should be notified.

The estimated total volume of blood that will be drawn from each patient in this study is presented in Table 2.

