**\* at selected sites only**

Laboratory values that fall outside a clinically accepted reference range must be evaluated and commented on by the Investigator, and graded according to the DMID Toxicity Scale for Determining Severity of Adverse Events (Attachment 7). Generally, clinically significant abnormalities that represent a change from baseline and could be considered to be detrimental are to be recorded as adverse events. It is anticipated that a fall in haematological parameters such as haemoglobin may occur during treatment and, in general falls of up to 2 g/dL need not be reported as adverse events unless that fall is considered to be detrimental to the patient. Detrimental changes in differential white cell count (other than clinically significant falls in neutrophils) should only be reported as adverse events

if their change is considered to be contributing to deterioration on the patients' condition.

Investigators must document their review of each laboratory report by signing and dating each report. Laboratory data will be transcribed into the CRF. The laboratory reports are to be kept with the CRF until source data verification has been performed by the monitor and then it should be filed with the source document for the study.

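### The laboratory shift summary, built on normal ranges, shows no shift when a patient who enters abnormal worsens to a severe grade; shifts in DMID grade would be a cheap, optional addition

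*Protocol*

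**What the plan says.** Section 9.5.2 (Laboratory Data) plans three outputs. The first is a table of patient incidence: any "clinically significant abnormal value as reported by the Investigator will be provided by lab parameter, treatment group and scheduled visit". The second is a summary of shifts from baseline to each later visit, for which "Normal ranges will be used to determine if a laboratory value was normal or not". The third is descriptive statistics for every safety parameter.

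Section 3.2.2 excludes "Liver function tests (AST/ALT levels) more than 2.5 times the upper limit of normal range", and "Presence of significant anaemia, as defined by" a haemoglobin below 8 g/dL. It sets no numeric limit for platelets, neutrophils or bilirubin, and the Entry Laboratory Screen does not require those three results before randomisation.

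Section 5.2.2 has the investigator evaluate out-of-range values and grade them on the DMID scale in Attachment 7. For haemoglobin it adds, as a default rule, that "falls of up to 2 g/dL need not be reported as adverse events unless that fall is considered to be detrimental to the patient". Section 9 as a whole is described as a summary, with detail left to an SAP that was not available for this review.

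**The concern.** A shift table that sorts values only by normal range records a change when a patient crosses a limit of normal. Someone already outside that limit at baseline cannot cross it again in the same direction, so further deterioration, however large, leaves the patient in the same cell. The entry criteria expressly admit such patients for haemoglobin and transaminases.

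These parameters matter for this product. The Toxicology section of the Introduction reports hepatic inflammatory changes with pyronaridine in the rat and reduced erythrocyte indices with both components, and section 5.2.2 expects haemoglobin to fall during treatment. Comparing safety is part of the primary objective (section 2). The DMID grades that would reveal the worsening are already to be assigned under section 5.2.2, but the laboratory analysis in section 9.5.2 does not use them.

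**Working it through.** The Protocol gives no figure of its own to reproduce on this point. The check applies the Attachment 7 cut-offs to the most abnormal baselines that section 3.2.2 admits.

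**Inputs (Attachment 7)**
- Adult haemoglobin, g/dL: Grade 1 9.5-10.5, Grade 2 8.0-9.4, Grade 3 6.5-7.9, Grade 4 below 6.5.
- Paediatric haemoglobin, g/dL: Grade 1 10-10.9, Grade 2 7.0-9.9, Grade 3 below 7.0. Grade 4 is cardiac failure secondary to anaemia, a clinical criterion.
- Adult ALT, x ULN: Grade 1 1.25-2.5, Grade 2 2.6-5, Grade 3 5.1-10, Grade 4 above 10.
- Paediatric ALT, x ULN: Grade 1 1.1-4.9, Grade 2 5.0-9.9, Grade 3 10.0-15.0, Grade 4 above 15.0.
- Adult platelets, per mm3: Grade 1 75,000-99,999, Grade 4 below 20,000.

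**Haemoglobin, adult scale (steps of 0.1 g/dL)**
- From the entry floor, 8.0 - 0.1 = 7.9 is Grade 3 and 8.0 - 1.6 = 6.4 is Grade 4.
- With a fall of at most 2.0, the highest baseline that can reach Grade 3 is 9.9 (9.9 - 2.0 = 7.9), and the highest that can reach Grade 4 is 8.4 (8.4 - 2.0 = 6.4).
- So adults entering at 8.0-9.9 can reach Grade 3 or worse, and those entering at 8.0-8.4 can reach Grade 4, without passing the 2 g/dL reporting threshold.

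**Haemoglobin, paediatric scale**
- 8.0 - 1.1 = 6.9 is Grade 3.
- Within a fall of 2.0 the highest baseline that can reach Grade 3 is 8.9 (8.9 - 2.0 = 6.9).

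**ALT**
- From 2.5 to 12 x ULN is a 12 / 2.5 = 4.8-fold rise: adult Grade 1 to 4, paediatric Grade 1 to 3.
- Adult Grade 3 already starts at 5.1 / 2.5 = 2.04 times the entry limit.

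**Platelets, adult scale**
- From 90,000 to 19,000 is Grade 1 to 4.

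**Reading the shift table.** Under a normal/abnormal or a low/normal/high layout, every one of these patients is in the same category before and after. The ALT example needs no further assumption, since 2.5 x ULN is above normal by definition. The haemoglobin and platelet examples assume that the laboratory's lower limit of normal lies above the baseline value. The Protocol gives no limits, but DMID Grade 1 haemoglobin extends up to 10.5 (adult) and 10.9 (paediatric) g/dL, and adult Grade 1 platelets up to 99,999.

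**The case against.** Four arguments stand on the other side.

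First, graded laboratory tables are ordinary SAP content, and section 9 says it is only a summary. A reader might infer that the trial will have no objective count by arm of patients worsening to a severe grade. The Protocol does not support that: it names no such count, but the unseen SAP may contain one, so the absence is not a finding.

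Second, the sentence on normal ranges defines normality correctly and does not say that the table has only two categories. That is true. But neither natural layout (normal/abnormal or low/normal/high) separates mild from severe abnormality. A further category for clinical significance, which the wording would permit, would show the worsening only where the investigator made that judgement.

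Third, severe worsening has other ways to appear: the incidence of clinically significant values, which carries no 2 g/dL exemption; adverse events by worst severity grade; possible serious status on grade deterioration (section 5.2.4.1); and minima and maxima (section 9.1). A reader might infer that severe deterioration would be hidden, or hidden more in one arm. Neither follows. An investigator who has just graded an ALT of 12 x ULN as Grade 4 is unlikely to call it insignificant, the haemoglobin exemption lapses if the fall is judged detrimental, and the judgement is made blind to treatment. What remains is narrower: the counting routes rest on judgement, and minima and maxima do not count patients.

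Fourth, entry has safeguards beyond numeric limits. Exclusion 4 bars clinically significant disorders, including hepatic ones. The Study Medical Monitor is also to be told where "baseline laboratory evaluations of other haematology, biochemistry and urine parameters fall outside of the normal range", if this is judged clinically important. This reduces the number of patients with marked baseline abnormality but does not touch haemoglobin of 8 g/dL and above or AST/ALT up to 2.5 x ULN, which the criteria admit.

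**Conclusion.** The point holds in a limited form. The shift summary as stated cannot display further worsening in patients who enter abnormal, up to and including DMID Grade 4, and for haemoglobin some of those falls are also exempt by default from adverse event reporting. Because investigator-judged clinically significant values and graded adverse events should catch most such cases, this is an optional improvement to a supplementary safety display, not a flaw that puts the safety comparison in doubt. The efficacy analysis and the sample size are unaffected.

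The size is shown by example only. The Protocol gives no baseline distribution and no rate of severe worsening, so no number of affected patients can be stated. The conclusion rests on a shift table laid out by normal range alone and, for haemoglobin and platelets, on the assumption about lower limits of normal given above.

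**What to change.** Keep the planned table. In the Protocol or SAP, add by arm a shift from baseline DMID grade to worst post-baseline DMID grade for ALT, AST, bilirubin, creatinine, haemoglobin, neutrophils and platelets, with the number of patients worsening to Grade 3 or 4. Three details should be fixed with it:

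- Derive the grades from the recorded values and include unscheduled ones. Section 5.2.2 provides for them: "Haematology parameters are to be measured on Days 0, 3, 7, 28 and 42 and, if clinically indicated, on other visits".
- State the age at which the adult scale replaces the paediatric one. Attachment 7 gives no general cut-off, its creatinine age bands do not settle the matter, and the choice has consequences: ALT Grade 3 starts at 5.1 x ULN on one scale and 10.0 x ULN on the other.
- Report paediatric haemoglobin as Grade 3 or higher (below 7.0 g/dL), since a laboratory value cannot establish its Grade 4.

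The cost is a sentence or two and a few tables. Laboratory results are already transcribed into the CRF, so no new data are needed. If the SAP already contains these tables, nothing further is required.
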